**Enrollment**					
Informed consent		x			
Assent		x			
Allocation		x			
**Intervention**					
School-based sexual education intervention					
**Assessments**					
Socio-demographic	Personal and home information (ad hoc survey)		x		
	Social network information		X		
Knowledge about sexuality; preventive behavior in sexuality and behavioral intention; empowering and self-efficacy	Knowledge test [46, 47] Survey ad hoc		x	x	x
Gender attitude	Scale of detection of sexism in adolescents (DSA) [48]	x	x	x	x
	Scale of negative attitudes towards trans persons [40]	x	x	x	x
	Short version of Modern Homophobia Scale [41]	x	x	x	x
Mental health	PSC-17 [42]	x	x	x	x

The enrollment, intervention, and assessments are shown in Table 2.

In each intervention session, we will record the attendance and duration, and using structured observation [49], we will record some elements referring to the implementation of the intervention. Those responsible for executing the intervention will receive bi-monthly supervision to control the evaluation and retention.

No specific retention strategy is planned. Available information for students who drop out will include their socio-demographic data, the number of sessions attended, and the results obtained in the tests administered before dropping out.

Because it will be a mixed experimental design GRTs, at the end of the intervention, we will perform a qualitative Case Study to ascertain the experience of the participants and executors with respect to the program and its implementation. Each school of the study group will be a case. The participants will be students who participated in the program and the executors who implemented the intervention. Each case will include focus groups with the students (at least one per case) and semi-structured interviews with the executors (at least two per case). We will then perform a Qualitative Content Analysis to identify certain emergent topics.

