### Participants: eligibility criteria

The intervention will be directed exclusively to students of the 10^th^ and 11^th^ grades who are enrolled in one of the education establishments that depend on the Municipality of Santiago. The inclusion criteria for these schools will be the following: (i) have students of these grades enrolled; (ii) not being an education center oriented to adults or persons deprived of liberty (e.g., closed or semi-closed compounds of Gendarmería de Chile or the National Service for Minors); (iii) have regularity in teaching and learning (for example, schools that were not partially interrupted in 2022 by student manifestations); and (iv) have informed consent of the director. The inclusion criteria for the students will be (i) having 90% or greater attendance in classes: (ii) providing informed consent of voluntary participation; and (iii) having explicit and informed consent of their parents or guardians.

The selected students will be randomly divided into the study and control groups; the intervention will take place in the same schools that the students attend. The assignment to groups will use simple random sampling, performed in two stages. In the first stage, the available schools will be randomly assigned to the study and control groups, while the second stage will randomly select the groups in each school that will participate. The study groups will receive a 10-session intervention in sexual education, covering topics related to preventive sexual conduct, gender equity, and mental health. The control groups will not receive intervention; they will continue with the sexual orientation that each school provides to its students. Sexual orientation is general and is provided by the Ministry of Education. The goal is to evaluate and diagnose the behaviors and reproductive health needs of adolescents, addressing the values adopted regarding the decision to engage in sexual relationships and/or have multiple sexual partners, as well as perceptions of risk.

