### Awareness of assignment

Before starting the study, collaboration agreements will be signed with the institutions interested in receiving the designed intervention. Subsequently, after identifying the study sites, their consent to participate in the study will be obtained.

Once the schools, courses, and students who will participate in the study have been defined, the school principals, teachers, and students will be contacted to explain the objectives of the intervention, the way it will be performed, and the measurements that will be taken. Since the evaluation instruments will be answered online, the students will be contacted by telephone or WhatsApp to ensure both their participation and follow-up. The final follow-up of the cohort is tentatively scheduled for August 2024.

Since the GRTs is a mixed experimental design, the next phase will evaluate the implementation of the program, in order to analyze how the implementation of a comprehensive, preventive program of sexual health facilitates or impedes a gender-transformative intervention. For this we will conduct semi-structured interviews with those persons who will perform the intervention (teachers, psychologists or guidance counselors) and focus groups of students who participate in the intervention.

These techniques will allow collating and triangulating the results and exploring the particulars of each case, which will complement the findings of the GRTs. The interviews and focus groups will approach the relations between different dimensions of the implementation process and the results experienced by the participants from the gender-transforming approach (benefits for adolescent females, males, and LGTB students, changes in gender norms and stereotypes, among others).

Finally, since this is a mixed study, the information from the experimental phase and implementation will be integrated. This implies analyzing the qualitative results of the trial and then determining how the qualitative results empower the trial [23]. Thus the results obtained from the GRTs may be explained using the information from the experiences of the participants about the implementation process of the program.

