Based on the nature of this trial, no relevant concomitant care is required. There is also no specific treatment allowed or prohibited during the trial. Similarly, no particular retention strategy is foreseen, and no special criteria exist for interrupting or modifying the assigned interventions.

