### Outcomes

Before implementing the workshop, we will perform a base-level measurement of the variables in the students. Later we will measure the result variables in two moments, just after the workshop closes and 3 months after the closure, in order to evaluate the results obtained by the intervention, to determine the effect of the program.

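### The data rule for students who drop out does not separate stopping the sessions from leaving the study, which leaves a route to outcome loss that only the study arm has

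*Protocol article*

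**What the plan says.** All references are to the protocol article.

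- **Outcomes, text after Table 2.** For students who drop out, the information available is socio-demographic data, "the number of sessions attended, and the results obtained in the tests administered before dropping out". The same paragraph says: "No specific retention strategy is planned".
- **Participants: eligibility criteria.** "The study groups will receive a 10-session intervention in sexual education". By contrast, "The control groups will not receive intervention; they will continue with the sexual orientation that each school provides to its students".
- **Outcomes, opening paragraph.** After baseline, outcomes are measured "just after the workshop closes and 3 months after the closure".
- **Trial design and Awareness of assignment.** The questionnaire is a web survey whose link goes to each participant, and "the students will be contacted by telephone or WhatsApp to ensure both their participation and follow-up". Neither section limits this by arm or by attendance.
- **Analytical methods.** Missing data are not imputed. Separately, to deal with poor adherence, it is suggested that students who miss more than 30% of the sessions be left out of the analysis.
- **Ethics.** Any participant may withdraw from the study at any time.

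**The concern.** The sentence on dropouts describes them partly by how many sessions they attended, and the only test results it lists are those obtained before they left. It does not say whether dropping out means no longer coming to the workshop or no longer taking part in the study. Staff reading it could reasonably stop sending questionnaires to a student who has left the workshop but is still enrolled and reachable.

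A control student has no programme sessions to leave. On that reading the study arm has an extra way of losing outcomes. The outcomes include sexism, attitudes toward trans and homosexual persons, and mental health, and leaving a programme on gender and sexuality may be related to them. What is at stake is whether the arms can be compared as allocated. An analysis-set rule can be reversed while the data exist, but a questionnaire that was never sent cannot be recovered.

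**Working it through.** The article states no dropout rate, so there is no figure to reproduce. The check sets the passages side by side under the two possible meanings of dropping out.

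**Step 1. Trace one student.** Take a study-arm student who attends sessions 1 to 4 of 10, then stops, and remains enrolled at the school.

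| | Dropping out = leaving the sessions | Dropping out = leaving the study |
|---|---|---|
| Data on this student | Baseline only, since both outcome times fall after the workshop closes | Baseline, post and 3-month questionnaires all due |
| Control counterpart | Has no sessions to leave; both questionnaires due | Same rule as in the study arm |
| Loss route specific to one arm | Yes, study arm | No |

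The reference to sessions attended points to the left column. The link sent to each participant, the general follow-up contact and the right to withdraw from the study point to the right column. The text does not settle it.

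**Step 2. Check against the attendance exclusion.** With 10 sessions, 30% is 0.30 × 10 = 3, so the exclusion applies from the fourth missed session.

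- Stopping after session 4 means 10 − 4 = 6 missed, 6/10 = 60%. This student is excluded from the suggested analysis even if both questionnaires are returned.
- Stopping after session 7, 8 or 9, with full attendance until then, means 3, 2 or 1 missed, or 30%, 20% or 10%. None exceeds 30%. These students stay in the analysis set, yet under the left column they have no outcomes.

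So the two rules overlap but are not the same. Changing only the collection rule would not bring the session-4 leaver into the planned analysis. Changing only the analysis rule would not produce outcomes that were never sought.

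**Step 3. Can a size be derived?** Let p be the fraction of an arm whose outcome is lost, and g the mean change from baseline in those lost minus the mean change in those retained. The arm mean is the retained mean plus p × g, so analysing only those retained shifts the study-minus-control contrast by

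shift = p(control) × g(control) − p(study) × g(study).

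The shift is zero when losses and gaps are equal in the two arms. The article gives none of the four quantities. The outcomes are defined as changes, so g has to be a difference in change. A stable difference in level between leavers and stayers is present at baseline and at follow-up alike, and largely cancels. Neither the size nor the sign of the shift follows from the document.

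**The case against.** The strongest case on the other side is that the sentence describes what information will be available and does not order collection to stop. Its list need not be exhaustive. Analytical methods treats poor attendance separately as non-adherence, and a rule excluding low attenders would have little purpose if they never had outcomes. The link goes to each participant, contact is planned for students in general, and both arms may withdraw. The article also condenses a fuller protocol, where a definition of dropout might stand. All of this holds against certainty. It does not remove the point, because the article does state a data rule for dropouts and that rule can be read in two ways with different consequences for one arm.

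Three stronger readings are tempting, and the document does not support them.

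- **That outcomes will be lost selectively in the study arm.** No passage says that a student who stops attending gets no further survey. Control students can also withdraw or ignore a web questionnaire, and a student who leaves after the post test loses only the 3-month result.
- **That the bias can be expressed as a share of the 0.2 points in Sample size.** This needs assumed attrition rates, an assumed gap in change, and a reading of 0.2 as standardised, which that section does not state.
- **That the statements on retention contradict each other.** The article says "no particular retention strategy is foreseen", yet plans follow-up contact with students and gives those running the sessions "bi-monthly supervision to control the evaluation and retention". Having no dedicated strategy is compatible with ordinary contact to deliver a survey and with supervision of staff. The wording is loose, but the conflict is weak.

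**Conclusion.** The point holds as a risk. As written, the plan lists only earlier tests for dropouts, leaves dropping out undefined, plans no specific retention strategy and rules out imputation, while sessions exist in one arm only. Post-intervention and 3-month outcomes can therefore be lost through a route that the control arm lacks, with a risk of differential attrition bias.

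This rests on the reading that leaving the sessions may be handled as dropping out, which the reference to session counts suggests but does not establish. If dropping out means leaving the study, the rule is the same in both arms and this route closes. The size and direction of any bias cannot be derived, and no figure should be attached to it. The change is still worth making, because uncollected outcomes are irrecoverable and the means of collecting them are already planned.

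**What to change.** Replace the sentence on dropouts in Outcomes with a rule along these lines: a student who stops attending sessions stays in the study; the post-intervention and 3-month questionnaires are sent to every enrolled student in both arms regardless of attendance, through the web link and the WhatsApp or telephone contact already planned, with the same follow-up contact in both arms; collection stops only when consent to be surveyed is withdrawn, and that withdrawal is recorded with its date.

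In Analytical methods, state that the main comparison uses these data as allocated, so that the exclusion of students missing more than 30% of sessions does not remove them from it. Without this second change, the outcomes newly secured from most early leavers would not enter the planned analysis.

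The cost is a change of wording and some extra messages or calls. The survey link and the contact channels are already part of the plan.

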### Analytical methods

The information that results from the application of the scales will be summarized with descriptive statistics (frequency table, mean, standard error, and asymmetry coefficient) for the pre- and post-intervention evaluations.

Since the intervention has specific objectives for each session, it is not appropriate to impute missing data. However, to account for the potential lack of adherence by some students, it is suggested that participants who miss more than 30% of the sessions should not be included in the data analysis. Regardless of attendance, students will be able to participate in all workshop activities.

We will compare the three evaluations, incorporating information relative to the type of school and course. If the data are normally distributed, we will perform one-way ANOVAs, incorporating post hoc information of the results when necessary, and perform pair-wise comparisons using the Tukey or Games-Howell test.

After the variables with main effects are established, we will perform a factorial ANOVA, in which one of the factors will be fixed (i.e., type of school) and the other will be the repeated measures of the three evaluations. As well as evaluating if the main effects are sustained over time, this will evaluate possible interactions among the studied factors. In this case, following the guidelines proposed by Cohen^75^ for ANOVAs with two or more factors, the effect size will be reported as the partial Eta^2^ statistic. The interpretation of the effect sizes will consider the suggestions of Cohen [50]. These analyses will use the program Jamovi version 1.2 [51].

No interim data analysis will be conducted, and there will be no stopping guidelines.

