### Allocation process

The allocation sequence will be generated using random numbers produced by the statistical program R. A single investigator will carry out both the sequence of participants’ assignments and their assignment to each group ([name]).

To ensure a blind analysis, the professional in charge of data analysis ([name]) will not know to which group the participants belong. Therefore, the database will be anonymized by assigning codes, which will only be known by another team professional ([name]). Unmasking is not considered to be permitted under any circumstances.

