### Intervention: description of Focus-on

Focus-on is a comprehensive program of sexual education for adolescents. Its design follows the guidelines of the Intervention Mapping Approach [26] and the orientations proposed by the Framework for Gender-Transformative Health Promotion [16]. Specifically considered are (i) the theories, contents, and strategies of the randomized controlled trial of comprehensive interventions for adolescents performed in the last 10 years [27]; and (ii) the results of a previous study in the object population on the implementation of an intervention in sexual health education. Both studies were done by the team that created the program.

The program is based on three fundamental theories as transverse axes: the Theory of Planned Behavior [28], the Framework for Gender-Transformative Health Promotion [16], and the Ecological Focus of Human Development [29]. Some sessions will use the precepts of the Theory of Social Learning [30], the Cognitive-Behavioral Theory using the emotion-regulating model of Gross [31], and the Transtheoretical Change Model [32].

The intervention has a participative focus, thus the activities are designed to promote processes of knowledge, understanding, application, analysis, and reflection in the adolescents. The activities aim to improve the capacity for critical thinking, favor the retention and communication of the new information, increase the motivation to listen and learn actively, and to improve interpersonal abilities. The execution of the intervention uses three pillars: (i) preventive sexual behavior; (ii) gender equity; and (iii) mental health. These pillars approach their different objectives -promote preventive sexual behavior, gender equity in sexual health, and improve aspects of mental health related to sexuality.

The intervention consists of ten weekly sessions, each lasting 1 h, which (except the first, which is an introduction to the program) treat these pillars gradually, from the basic to the most advanced aspects. The teams that will perform the intervention will be composed of at least two professionals of the psychosocial area (mainly psychologists, social workers, and/or guidance counselors) of the schools included in the study, who will be capacitated in the correct implementation of Focus-on.

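### The attendance rule excludes students from the study arm only, after randomisation, and no analysis of all students as randomised is given

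*Protocol article*

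**What the plan says.** The protocol article's Analytical methods section deals with missing data and adherence together. Because each session has its own objectives, it holds that "it is not appropriate to impute missing data". To allow for poor adherence, it then suggests that "participants who miss more than 30% of the sessions should not be included in the data analysis". No other analysis set is named. The analysis of the three evaluations is a set of ANOVAs, ending in a factorial ANOVA with the three evaluations as a repeated measure.

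Three other places show where the rule can act:

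- Intervention: description of Focus-on: "The intervention consists of ten weekly sessions, each lasting 1 h".
- Participants: eligibility criteria: "The control groups will not receive intervention; they will continue with the sexual orientation that each school provides to its students".
- Outcomes, in the text after Table 2: "In each intervention session, we will record the attendance and duration". The same text adds "No specific retention strategy is planned", and says that test results obtained before a student drops out will be available.

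The stated main objective is to evaluate the effectiveness of the programme in schools.

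**The concern.** Randomisation makes the two arms comparable as allocated. A rule that depends on behaviour after allocation, and that can be applied in one arm only, undoes this. Students in control schools who would have skipped the sessions cannot be identified, so they remain. The study arm loses its least engaged students. What is left compares adherent study students with all control students, which is a different question from whether offering the programme in schools works. If engagement is related to how outcomes change, a difference between arms can appear with no programme effect at all.

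The missing-data sentence adds to the problem. Session-specific objectives are a reason not to impute attendance or exposure. They say nothing about the outcome questionnaires, which are answered online and scheduled for everyone at baseline, after the programme and at 3 months.

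**Working it through.** **Plan's own figures.** The plan gives no figure for expected exclusions or for their effect. Its sample size reproduces: with z = 2.58, 2.58² × 0.25 / 0.05² = 665.64, and 665.64 / (1 + 664.64/6518) = 604.05, rounded up to 605 (603 with the unrounded z). That figure makes no allowance for exclusions and does not bear on the point. The planned difference is 0.2 points with no SD.

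**Step 1: threshold.** 30% of 10 sessions is 3, so exclusion begins at 4 missed.

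**Step 2: where it applies.** Sessions, and therefore attendance records, exist only in the study arm (301 students in Table 1). The rule cannot remove any of the 308 control students.

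**Step 3: how many it removes.** Let a be the chance of missing any one session (an assumption), with independent absences. Share excluded p = 1 − Σ(k = 0 to 3) C(10,k) aᵏ(1 − a)¹⁰⁻ᵏ. At a = 0.10 this is 1 − (0.3487 + 0.3874 + 0.1937 + 0.0574) = 0.0128.

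**Step 4: bias with no true effect.** Mean(retained) − mean(all) = p × δ, where δ is the retained-minus-excluded difference in the analysed outcome. This is an identity. The values δ = 0.3 and 0.5 SD are assumptions.

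| Session absence a | Share excluded p | Students of 301 | Bias, δ = 0.3 SD | Bias, δ = 0.5 SD |
|---|---|---|---|---|
| 10% | 1.3% | 4 | 0.004 | 0.006 |
| 15% | 5.0% | 15 | 0.015 | 0.025 |
| 20% | 12.1% | 36 | 0.036 | 0.060 |
| 25% | 22.4% | 67 | 0.067 | 0.112 |
| (p set directly) | 30% | 90 | 0.090 | 0.150 |

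**Step 5: cross-check.** If attendance and outcome are jointly normal with correlation ρ, and the lowest-attending share q is removed, the bias is ρφ(z_q)/(1 − q). With ρ = 0.3 this gives 0.010, 0.058, 0.105 and 0.149 SD at q = 1.3%, 10%, 20% and 30%, the same order as the table. A stronger link gives more: 0.248 SD at q = 30% and ρ = 0.5.

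**Step 6: missing waves.** The article does not say that students with a missing questionnaire are dropped. A classical repeated-measures ANOVA over three evaluations, without imputation, needs all three, so in practice they would be. The pre-dropout results that the article says it will hold then have no stated use.

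**The case against.** Several objections have force.

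- *Few may be excluded.* Entry requires at least 90% class attendance. If session attendance matches that and absences are independent, about 4 of 301 students are lost and the bias is negligible. This stands as a possible case. However, absence may cluster, students may withdraw at any time (Ethics), and the plan sets no limit.
- *Outcomes are defined as changes.* Stable differences between good and poor attenders largely cancel in change from baseline, so δ must be read as a difference in change. This stands and lowers the likely size.
- *The rule is only suggested, and an SAP may say more.* The wording is soft, but the rule is the only analysis set that the article states. The point rests on what is written, not on something left out.

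A reader might also infer more than the documents support:

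- *That the result is certainly biased towards the programme.* Nothing in the article links attendance to outcome. The direction would reverse if poor attenders would have done better.
- *That the bias is a given fraction of the target effect.* The target is 0.2 points with no SD, so a bias in SD units cannot be expressed as a share of it.
- *That the rule unblinds the analyst,* who "will not know to which group the participants belong". It would do so only if the analyst sees attendance. The professional who holds the codes could apply the rule before handing over the data.
- *That a complier-average estimate at the 70% cut-off would be a sound replacement.* It would require that attending one to six sessions has no effect, which is hard to accept when each session has its own objectives.

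**Conclusion.** The point holds as a design fault in the analysis set: a post-randomisation exclusion that can operate in one arm only, with no analysis of all students as randomised, in a trial whose aim is effectiveness. This follows from the text and needs no assumption.

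The direction is probable, not proven. The size is unknown: about 0.004 SD if 1.3% are excluded and δ is 0.3 SD, up to 0.15 SD if 30% are excluded and δ is 0.5 SD, with smaller values where change from baseline removes stable differences. These figures rest on assumed absence rates, independence of absences and assumed δ. Even if the bias proves small, the stated reason against imputation does not fit the questionnaires.

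**What to change.** Make the primary analysis all randomised students by allocated arm, whatever their attendance. Use every available questionnaire wave, for example in a mixed model with a school effect, and add a sensitivity analysis for missing data. Replace the session-objectives argument with a rationale that concerns the questionnaires themselves. State that students with poor attendance remain due for the post-programme and 3-month questionnaires; nothing in the article prevents this, and telephone or WhatsApp contact is already planned. Keep the more-than-30% rule only for a supplementary adherence analysis, labelled as such.

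The cost is a change of text, a little more analysis work and a possibly smaller effect estimate. No new data collection is needed.

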**Methods:**

We will use a mixed method experimental design with a parallel cluster-randomized trial (GRTs) that will evaluate the effectiveness of a comprehensive gender-transformative intervention of sexual education (ENFOCATE -Focus-on-), which will be complemented with qualitative studies to understand the implementation process. The participants will be 609 10^th^ and 11^th^-grade students. The randomization will be by grade, and the data will be collected at three moments (pre-intervention, post-intervention, and a 3-month follow-up).

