## Methods

### Trial design

We propose a mixed method experimental design [23] with a parallel cluster-randomized trial (GRTs) that will evaluate the efficiency of intervention and implementation of a comprehensive gender-transformative sexual education, along with qualitative studies to understand the implementation process. The results of the intervention will be evaluated after it finishes, and in a 3-month follow-up. Each participant will be sent a link to the questionnaire (web-based survey). Follow-up contact will be done with WhatsApp or telephone calls. The protocol of the study is drafted following the Standard Protocol for a randomized trial of a social or psychological intervention (CONSORT-SPI). Figure 1 is a general flow chart of the procedure (supplementary material 1 includes the SPIRIT checklist).

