### Study setting

Interventions will be performed in 10 schools financed by the State located in the commune of Santiago (Metropolitan Region, central Chile), which is the third-most populous commune according to the latest country census.

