### Randomization

The assignment of the participants to the groups will be implemented in a two-stage selection of the students; since there are already existing teaching-learning processes in process in the schools, with their time limitations, we will have to choose entire “courses” (in Chilean secondary schools, a course is a group of about 40 students who have all classes together) rather than choose individual students.

We will establish groups among the schools to compensate for their different sizes; some schools in the commune are much larger than others (four or more courses per grade. Thus, we will divide the schools into two blocks: one with the largest schools and one with the medium- and small-sized schools. In the second stage, courses that meet the inclusion criteria to participate in the study will be selected randomly within each block. Table 1 details the distribution of the samples.

**Table 1 Tab1:** Samples to be selected

	**Study group** **No. of students per grade**		**Control group** **No. of students per grade**		
**School**	*10th grade*	*11th grade*	*10th grade*	*11th grade*	Total
*1*	---	---	31	28	59
*2*	---	---	33	27	60
*3*	---	---	34	34	68
*4*	---	---	26	30	56
*5*	---	---	33	32	65
*6*	29	27	---	---	56
*7*	29	30	---	---	59
*8*	28	29	---	---	57
*9*	25	31	---	---	56
*10*	*40*	*33*	---	---	73
	151	150	157	151	
**Sample totals**	**301**		**308**		**609**

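### Whole schools are randomised, but the stated ANOVAs treat students as independent, so the arm comparison can exceed its nominal 5% error rate

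*Protocol article*

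**What the plan says.** Trial design calls the study "a parallel cluster-randomized trial (GRTs"). Participants: eligibility criteria gives the first step of allocation: "In the first stage, the available schools will be randomly assigned to the study and control groups". Study setting adds: "Interventions will be performed in 10 schools financed by the State". Table 1 shows schools 1 to 5 only in the control group (308 students) and schools 6 to 10 only in the study group (301 students).

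Other places word the unit differently. The Abstract says "The randomization will be by grade". The Randomization section says that existing timetables mean "we will have to choose entire “courses", selected at random within two blocks defined by school size.

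For the outcomes, Analytical methods states: "If the data are normally distributed, we will perform one-way ANOVAs, incorporating post hoc information of the results when necessary, and perform pair-wise comparisons", using Tukey or Games-Howell. It says that school type and course will be taken into account, without saying how. Variables that show main effects then go into a factorial ANOVA with school type as the fixed factor and the three evaluations as the repeated factor. The section names no random effect for school or course, no school-level summary and no robust variance. It also does not name study versus control as a factor. The Sample size section bases power on an ANOVA comparing two groups of students, with no ICC or design effect.

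**The concern.** When each school sits wholly in one arm, arm varies only between schools. Ten schools give 9 degrees of freedom between schools: 1 for arm and 8 for schools within arm. The valid error term for arm is the variation among schools within arm. The stated ANOVAs use variation among some 600 students instead.

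Pupils of one school share staff, climate and intake. In the study arm they also share the delivery team, which the protocol draws from each school's own psychosocial staff. If schools differ for such reasons, a student-level test counts part of that difference as programme effect. A chance imbalance between two sets of five schools could then be reported as effectiveness on any of the four hypothesised outcome domains. It could also decide which variables go forward to the factorial ANOVA.

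**Working it through.** **Inputs from the protocol.** School sizes in Table 1: 59, 60, 68, 56, 65 (control) and 56, 59, 57, 56, 73 (study); total 609. Alpha 0.05, N = 605, expected difference 0.2 points, claimed power at least 0.8 (Sample size).

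**Assumed, because the protocol does not give them.** ICC from 0.005 to 0.05; arm as the one-way factor (implied by Sample size, not named in Analytical methods); for power only, 0.2 points read as 0.2 SD.

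**1. The plan's own figures.** For 99% confidence and a 5% margin, n0 = 2.58² × 0.25 / 0.05² = 665.6. The finite-population correction for 6518 students gives 665.6 / (1 + 664.6/6518) = 604, close to 605. Power at N = 605 depends on how 0.2 points is scaled: 0.69 for 0.2 SD two-sided, 0.79 one-sided, 0.85 for a repeated-measures between-group test (f = 0.1, three measures, correlation 0.5), and above 0.99 for Cohen's f = 0.2. The claim of at least 0.8 is therefore reachable under some readings, but none of them includes clustering.

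**2. Design effect.** The size-weighted mean cluster is m = Σn²/Σn = 37,397/609 = 61.4, and DE = 1 + (m − 1) × ICC. The naive standard error is too small by a factor √DE.

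**3. True type I error of the student-level test.** This is 2 × [1 − Φ(1.96/√DE)]. For ICC 0.02: DE = 1 + 60.4 × 0.02 = 2.21, √DE = 1.49, 1.96/1.49 = 1.32, giving 0.19. The simulation used the Table 1 sizes with no true effect, 40,000 runs per ICC.

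| Assumed ICC | DE | √DE | Type I error, formula | Type I error, simulation |
|---|---|---|---|---|
| 0 | 1.00 | 1.00 | 0.050 | 0.048 |
| 0.005 | 1.30 | 1.14 | 0.086 | 0.083 |
| 0.01 | 1.60 | 1.27 | 0.122 | 0.123 |
| 0.02 | 2.21 | 1.49 | 0.187 | 0.190 |
| 0.05 | 4.02 | 2.01 | 0.328 | 0.334 |

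In the same runs, a t-test on the ten school means (8 df) held 0.049 to 0.052.

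**4. If courses were the only clusters.** Reading each cell of Table 1 as one course gives 20 clusters with size-weighted mean 30.8. At ICC 0.005, DE = 1 + 29.8 × 0.005 = 1.15 and the error is about 0.07. At 0.01, 0.02 and 0.05 it is 0.085, 0.12 and 0.21.

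**5. Change over time.** The same formula applies to change scores, with the ICC of the change. A simulation of the pooled t-test on change scores (Table 1 sizes, 20,000 runs) gave 0.087, 0.122, 0.185 and 0.333 at change-score ICCs of 0.005, 0.01, 0.02 and 0.05. That test is equivalent to a two-visit arm×visit test in a model with random intercepts only, because intercepts cancel from a between-visit contrast.

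**6. Power under a valid analysis.** For 0.2 SD with 8 df, power is 0.40, 0.31 and 0.19 at ICC 0.01, 0.02 and 0.05. The difference detectable with 80% power is 0.33, 0.39 and 0.52 SD.

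**The case against.** *This is a condensed article, and detail may sit in an analysis plan.* That would answer an omission. Here the section names the tests, the post hoc procedures, the fixed factor, the effect-size statistic and the software. It has fixed a method, and the method does not fit the declared design.

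*The section does take school type and course into account.* School type is a category; schools of one type remain separate clusters. Entering school itself as a fixed factor would not work either, since Table 1 aliases arm completely with school.

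*Repeated measures deal with correlation.* They deal with correlation within a student, not between students of one school.

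*The size is unknown.* This stands. A reader might infer that false-positive rates in this trial will be far above 5%. The protocol does not support that, because it gives no ICC. At 0.005 the error is only about 0.09, and the ICC of change scores, which is how the protocol frames its outcomes, may be lower than that of the scores.

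*The test and the unit are not pinned down.* This also stands. The calculation does not describe a one-way ANOVA whose factor is evaluation time. Table 1 and the eligibility section point to schools as the unit, but the Abstract and the Randomization section word it differently, and with courses as the only clusters the inflation is smaller.

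A reader might also infer that the claimed power is a miscalculation. Without an SD that cannot be shown; what can be said is that the calculation makes no allowance for clustering.

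**Conclusion.** The concern holds in conditional form. The stated ANOVAs do not match a design that assigns five whole schools to each arm. The standard error for study versus control is too small whenever outcomes, or changes in them, vary between schools; only an ICC of essentially zero would make the tests valid, and the protocol offers no support for that value. The four error rates from 0.09 to 0.33 rest on the assumed ICCs, on arm as the ANOVA factor and on school as the cluster. With courses as the only clusters the rates are lower but still above 0.05. Because the main objective is effectiveness and the correction is cheap, the analysis section should be changed before the outcome data are analysed.

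**What to change.** Name study arm as the factor of interest, state one unit of randomisation throughout, and make the target the baseline-adjusted arm difference at a named visit (post-intervention or 3 months). Then use one of two analyses:

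- **School-level:** compare baseline-adjusted means of the ten schools, with 8 df, or 7 if the school-size block is included (10 − intercept − arm − block).
- **Mixed model on the follow-up visits:** fixed effects for arm, visit, baseline score, grade and block; random effects for school, course and student; Kenward-Roger or Satterthwaite degrees of freedom.

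If arm×visit is tested, add school-by-visit and course-by-visit random effects, because random intercepts alone do not protect that contrast (step 5). Report the ICC and the adjusted difference with its 95% confidence interval.

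The cost is a rewritten section and modest programming; R is already used for allocation. No new data are needed. Intervals will be wider and power lower than the student-level calculation implies: even at ICC 0, the 8-df test has power 0.58 for 0.2 SD, against 0.69 for the student-level test. The Sample size section should say so, with an ICC stated.
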